#### Quantitative

The paired *t* test will be utilized to evaluate the statistical significance of the PSSUQ, SEQ, NASA-TLX, and performance (time taken for task completion and the number of errors committed) of participants using both the DCE and BWS within the prototypes for each group in all relevant phases. Analysis of variance tests will be utilized to evaluate whether statistical differences in the DCE and BWS occur across groups for these same measures. We will consider *P* values of less than .05 to have statistical significance, and 95% CIs will be used to establish differences between the DCE and BWS both within and across groups.

We aim to use the data from preassessments (demographics, geriatric assessment), in-person assessments (cognition, memory, and health literacy), digit span, and health records to determine predictor variables with patient treatment preferences, and to determine whether health literacy variance exists between patients and caregivers. Analysis of preassessments will include basic statistics (eg, mean, SD, and range).

All analysis will be performed in SAS JMP Pro (SAS Institute) for summarizing and grouping study results both between and across groups. We will work with an experienced statistician to ensure that we utilize appropriate methods and theories for data analysis.

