## Methods

### Study Design and Methodology

#### Overview

We will use a mixed methods research approach utilizing an iterative co-design approach. In phase 1 we will first conduct heuristic evaluations on each prototype to identify and improve existing usability issues. Usability testing will then be conducted in 3 stages: (1) with healthy volunteers to establish standards for validating the results of the target population; (2) with patients and caregivers to obtain subjective and objective feedback based on both their tacit knowledge and their novel experience using each prototype; and (3) with health care workers using qualitative assessments to gain insight into their overall impression of the tool as well as whether they would recommend this to patients and caregivers. Within phases 2-4, participants will evaluate visualizations on a Personalized Treatment Preferences Dashboard, which shows a visualization of the results a user would see upon completion of the choice tasks within the prototype. We will evaluate the prototypes and visualizations using qualitative assessments (think-aloud sessions and semistructured interviews) to develop an affinity diagram for thematic analysis, and quantitative assessments using validated questionnaires to evaluate the perceived usability of and the CWL required to perform tasks within the prototypes. This study will be conducted in iterative development stages, in which feedback from participants will be analyzed and incorporated into the design that will then be presented to subsequent groups, as depicted in Figure 1.

The involvement processes utilized in this study will be classified by the participatory co-design framework originally developed by Leinonen [31] and further refined, representing 4 distinct groupings: contextual inquiry, participatory design, product design, and software prototype as hypothesis (functional prototype) [32], as depicted in Multimedia Appendix 1. Evidence gathered from this study will be used to develop a functional prototype that effectively elicits and displays preferences, leading to more informed treatment decisions.

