### Participants and Setting

This study involves 4 participant types including healthy volunteers, patients, caregivers, and health care workers. Healthy volunteers will be recruited from the general population through the Research for Me at UNC platform and must be 21 years or older [36]. Patients who meet the following criteria will be eligible to participate: (1) have a confirmed diagnosis of a hematologic malignancy including leukemia, lymphoma, or myeloma; (2) be on active chemotherapy (not including maintenance therapy for myeloma); (3) be able to read and understand English; (4) age 60 years or older; and (5) be willing to provide consent. Caregivers must be (1) 21 years and older, and (2) identified as the primary caregiver by the patient. Health care workers must be employed within hematologic malignancies (inpatient or outpatient) units as a nurse, nurse navigator, advanced practitioner, or physician. Administrators that oversee patients with hematologic malignancy and have experience working with patients with AML will also be eligible. Exclusion from the study will occur if participants have dementia, altered mental status, or a psychiatric condition that would prohibit the understanding or rendering of informed consent or participation in the user testing.

We have chosen to include patients, caregivers, and health care workers in the design process to better understand patients’ physical characteristics, the mental characteristics of patients and caregivers, the needs and behaviors of all participants, as well as the sociotechnical context in which each participant engages with technology and manages treatment decisions [37]. The purpose of this EHT is to facilitate dialog among patients, caregivers, and health care workers, and therefore it is important to understand the perspective of each stakeholder, and identify related themes and insights that will be used to define the direction of the final prototype [37]. We have chosen to include healthy volunteers to both establish standards for validating our results as well as to identify usability issues before conducting testing with our target population. We intend to engage all stakeholders in the design process by inviting them to participate at levels that will promote empowerment in the shared decision-making process [38].

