##### Qualitative Assessments: Usability

Participants will perform think-aloud sessions throughout the user testing to share how each prototype has been able to capture their preferences for treatment outcomes or whether the display of preferences is useful. We will engage participants as co-designers, soliciting feedback on the available functions in the current prototypes and encouraging them to make suggested improvements to the design of the EHT as well as the visualization depicting user preferences. Information obtained during user testing will be aggregated per group and used for iterative improvements to the prototype. Each group will evaluate prototypes that have been revised based on stakeholder feedback from the previous groups.

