#### Phase 4: Final Evaluation of Usability, CWL, and Performance

##### Overview

Patients, caregivers, and health care workers will complete the preassessments as described in phase 3. Patients and caregivers will continue to participate in quantitative and qualitative assessments as described in phase 3, excluding the think-aloud sessions. In phase 4, patients and caregivers will also be asked to participate in task analysis and performance assessments of the DCE and BWS within the prototypes, including the evaluation of tasks using the Single Easy Questionnaire (SEQ), tracking time to complete, and the number of errors.

Health care workers will continue to participate as described in phase 3.

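### Across-phase comparisons of PSSUQ and NASA-TLX mix participant type, prototype version and think-aloud, so they cannot support population claims or make healthy volunteers a validating standard

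*Protocol article*

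**What the plan says.** All references are to the protocol article.

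- **Across-group inference** (Data Analysis, Quantitative): "Analysis of variance tests will be utilized to evaluate whether statistical differences in the DCE and BWS occur across groups for these same measures". The same paragraph says that "95% CIs will be used to establish differences between the DCE and BWS both within and across groups", and its significance threshold is P<.05. The measures are PSSUQ, SEQ, NASA-TLX, time and errors.
- **Revision between groups** (Phase 2, Qualitative Assessments: Usability): "Each group will evaluate prototypes that have been revised based on stakeholder feedback from the previous groups". The Overview under Study Design and Methodology applies this to the whole study: "feedback from participants will be analyzed and incorporated into the design that will then be presented to subsequent groups".
- **Role of volunteers** (same Overview): testing is done "with healthy volunteers to establish standards for validating the results of the target population". Participants and Setting says that they are included "to both establish standards for validating our results as well as to identify usability issues before conducting testing with our target population".
- **Test condition** (Phase 4, Overview): "Patients and caregivers will continue to participate in quantitative and qualitative assessments as described in phase 3, excluding the think-aloud sessions". Think-aloud is used in phases 2 and 3, and Table 1 agrees.

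**The concern.** Volunteers (21 or older) appear only in phase 2. Patients (60 or older) and caregivers appear only in phases 3 and 4. No version is frozen or shown to both populations. Moving from volunteers to patients thus changes both the people and the prototype. Moving from phase 3 to phase 4 changes the prototype and removes think-aloud.

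The article itself expects revision to matter. Phase 2 groups of five are meant to resolve about 75% of usability issues, and the Discussion anticipates improvements for phase 3 participants. Scores from superseded prototypes are a poor yardstick for scores on their replacements.

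The risk is that a significant across-phase result is published as a difference between patients and volunteers, or as proof that the revisions worked, when the data cannot tell these apart. A non-significant result is no safer, since the two effects can cancel. The Discussion acknowledges that the populations differ, but not that the prototypes they test differ as well.

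**Working it through.** The article gives no effect size, SD or power for the ANOVA, so there is no stated figure to reproduce. The check is whether the effects can be estimated.

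**Cells, in order of testing**

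| Version | Participants | Think-aloud |
|---|---|---|
| 0, 1, 2 | Volunteers, 3 groups of 5 | yes |
| 3, 4 | 10 patients + 10 caregivers in each of 2 groups | yes |
| 5 | Phase 4 patients and caregivers | no |

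One phase 4 group is an assumption, as the number is not stated. Health care workers give no quantitative data and are left out.

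**Estimability.** The columns are an intercept, 5 version terms, patient, caregiver and think-aloud: 9 in all. The rank is 7, because two relations are exact:

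- patient + caregiver = sum of the version indicators for phases 3 and 4;
- think-aloud = 1 − sum of the version indicators for phase 4.

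Both relations hold however many phase 4 groups there are, so the shortfall of two does not depend on that assumption.

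- *Not estimable:* volunteer versus patient; the think-aloud effect; the version step from the last volunteer group to the first phase 3 group.
- *Estimable:* version steps between groups of one phase; patient versus caregiver on the same version.

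With the version held constant, the model would have 4 columns and rank 4, and every effect would be estimable.

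**Size of the mixing (assumed trends).** The mean version index is (0+1+2)/3 = 1 for volunteers and (3+4)/2 = 3.5 for phase 3 patients, a gap of 2.5 revisions. With no population effect, a trend of d per revision gives a difference of 2.5d:

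- d = 0.1, 0.2, 0.3 SD gives 0.25, 0.50, 0.75 SD;
- d = 0.2 PSSUQ points gives 0.5 points, and 0.5/2.82 = 18% of the overall benchmark quoted in the article.

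**Behaviour of the F test.** One-way ANOVA on raw scores, groups of 5, 5, 5, 10, 10 (volunteers, then phase 3 patients), SD 1, alpha .05, 20,000 simulated trials, assumed effects:

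| Truth | Rejection rate |
|---|---|
| No effect | 5% |
| Version trend only, 0.3 SD per revision | 42% |
| Population effect only, 0.9 SD | 46% |
| Version +0.3 SD per revision, patients −0.9 SD | 13% |

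Two different truths give nearly the same rejection rate, and opposed effects largely hide each other.

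**DCE-BWS contrast.** The figures above are for raw scores. If DCE scores shift by a and BWS scores by b per revision, the contrast shifts by a − b per revision, so by 2.5(a − b) between volunteers and phase 3 patients. Equal revision gives 0. An assumed a − b of 0.1 or 0.2 PSSUQ points gives 0.25 or 0.50 points. The documents do not say how equally the two prototypes are revised.

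**The case against.** The best defence has four parts.

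1. **The study calls itself primarily descriptive, and its central comparison is within subjects with randomised order.** This stands. Each participant uses both prototypes at the same stage and under the same condition, so the paired test within a group is untouched. It lowers the severity, but the P<.05 tests and confidence intervals across groups remain in the plan.
2. **No sentence says that the ANOVA pools phases or sets volunteers against patients.** This is partly right. In the phase 2 and phase 3 sections a group is an iteration group within a phase. But the Quantitative section sets no such limit, and the standards role invites the wider comparison.
3. **Some across-group contrasts are interpretable.** This stands. Groups within a phase share participant type and think-aloud condition. A reader might infer that all across-group results are meaningless; the design does not support that.
4. **Not all measures are exposed.** This stands. Time and errors are collected only in phase 4. Table 1 and the Phase 4 Overview place the SEQ there too, although the phase 4 usability text says phase 3, which should be reconciled. Only PSSUQ and NASA-TLX clearly span phases.

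Two further inferences go too far. A reader might conclude that NASA-TLX scores taken with think-aloud would be wrongly judged against 55. The article cites 55 as background, plans no such test, and gives no figure for the effect of think-aloud. A reader might also compare the first volunteer group with the last phase 3 group: 4 revisions × an assumed 0.2 points = 0.8, or 28% of 2.82. That takes only the extremes, rests on an invented trend, has no SD behind it, and cancels from the DCE-BWS contrast if both prototypes improve equally.

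**Conclusion.** The concern holds for differences across phases in PSSUQ and NASA-TLX, and for the use of volunteers as a validating standard. Population, prototype version and, in phase 4, think-aloud are inseparable under any model, so an analysis plan could not repair this. Across-group differences in the DCE-BWS contrast are affected only to the extent that the two prototypes are revised unequally. The paired comparison within each group is sound, and change between groups within a phase is readable as a non-randomised iteration effect.

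The inseparability follows from the stated design and needs no numerical assumption. The sizes (0.25 to 0.75 SD; rejection rates of 42%, 46% and 13%) are illustrations under assumed trends, not estimates. Revising between groups is legitimate co-design; the fault lies in the inference drawn across phases. Severity: moderate.

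**What to change.** 1. **Data Analysis, Quantitative.** Limit across-group significance tests to contrasts within a phase: (a) successive groups of the same participant type, labelled as non-randomised iteration effects; (b) patients versus caregivers on the same version, analysed as pairs because they are enrolled as pairs, not by an independent-groups ANOVA. Report differences across phases descriptively, without P values and without attributing them to population.
2. **Study Design and Methodology (Overview) and Participants and Setting.** Remove the role of volunteers in setting standards for validation, and keep their role in finding usability problems before testing with the target population.
3. **Phases 2 and 3.** Keep the paired DCE-BWS comparisons, stating that each applies to the version tested. Let conclusions about the final prototypes rest on phase 4.

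The cost is a change of wording and fewer across-phase claims. No data collection changes.

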#### Qualitative

Qualitative data obtained through think-aloud sessions, interviews, and cognitive task analysis will be analyzed for each group and coded using thematic analysis [66,67]. Analysis of qualitative responses will include creating contingency tables and converting data into charts and graphs for identifying patterns and gaps. One-way contingency tables will be used to evaluate whether participants (1) found the prototypes challenging to complete, (2) understood the definitions of the attributes, (3) could distinguish between the attribute levels, (4) preferred either the DCE or BWS, and (5) felt patients or family caregivers would use this tool.

### Ethics Approval

This study, reference ID number 321807, received institutional review board (IRB) approval from the University of North Carolina Office of Research Information Systems in June 2021. It has been determined that the risk involved in this research is no more than minimal. This research requires annual UNC administrative review. Under the revised “Common Rule” of 2018, this study does not require continuing review and IRB approval will not expire. This study was reviewed in accordance with federal regulations governing human subjects research, including those found at 45 CFR 46 (Common Rule), 45 CFR 164 (HIPAA [Health Insurance Portability and Accountability Act]), 21 CFR 50 & 56 (FDA), and 40 CFR 26 (EPA), where applicable.

### Privacy and Security

We will do a chart review on patient electronic medical records, including age, race, treatment, and diagnosis. A message will be sent to the treating physician (oncologist) or principal investigator ([name]) to inquire as to whether the patient would be appropriate for the study.

The interview and usability testing will be conducted in the human factors laboratory that can be accessed only by the study team. In the laboratory, participants and researchers can work from their respective workstations, which are separated by glass and can communicate effectively using the devices available in the laboratory.

Health care workers will complete user testing via Zoom, which is HIPAA enabled through the UNC School of Medicine. The other questionnaires (eg, geriatric assessments) will be sent to the participants using REDCap, a secure web application. During the data collection in the laboratory, we will ensure that those not connected with this study are unable to see participants or hear the information that is shared. When reporting the research findings, data will be presented in a way that prevents individual participants from being identified.

This trial will be audited by the Lineberger Comprehensive Cancer Center data safety and monitoring committee every 6 or 12 months.

## Results

This study received approval from the Lineberger Comprehensive Cancer Center Oncology Protocol Review Committee in March 2021 and IRB approval from the University of North Carolina Office of Research Information Systems in June 2021. We began recruitment of healthy volunteers in August 2021. This study is expected to conclude in February 2023.

## Discussion

### Principal Findings

To the best of our knowledge, this study is the first to conduct comparative assessments of the usability, CWL, and performance between DCEs and BWS instruments when developed as an EHT. We designed this as a mixed methods study using an iterative co-design approach that includes healthy volunteers, patients, caregivers, and health care workers. One limitation of this methodology is that participants in phase 2 of this study are all healthy volunteers and likely have different life experience to our target population of older adults with hematologic malignancies. While our target population will likely experience the EHT differently than these volunteers, our study team anticipated that the findings from both qualitative and quantitative assessments would lead to usability improvements for phase 3 participants, which include patients and caregivers. This is consistent with previous studies that have first recruited healthy volunteers to effectively resolve usability problems prior to the definitive work with the target population [68,69].

### Dissemination

In December 2021, our findings from phase 2 were accepted for a publication in the conference proceedings in Springer Nature and for presentation at the virtual Human-Computer Interaction 2022 Conference [70]. Our study team is highly interdisciplinary; therefore, we aim to disseminate our findings across a more diverse audience within both medicine and health care engineering conferences and journals.

### Conclusion

Our findings will help differentiate the usability, CWL, performance, and alignment of patient preferences for both the DCE and BWS within the prototypes. This study has the potential for optimizing the collaboration and empowerment of older adults in the development of an EHT, improving elicitation of treatment preferences, and improving communication between patients and health care workers. Future research should continue to evaluate the levels at which older adults participate in the full development process, and how this can either limit or encourage their collaboration and empowerment.

## Appendix

Multimedia Appendix 1 Proposed involvement processes based on Leinonen's framework.

Multimedia Appendix 2 Proposed validated assessments.

## Abbreviations

AML: acute myeloid leukemia
BOMC: Blessed Orientation Memory Concentration
BWS: best-worst scaling
CIRS-G: Cumulative Illness Rating Scale-Geriatric
CWL: cognitive workload
DCE: discrete choice experiment
eHEALS: eHealth Literacy Scale
eHEALS-Carer: eHealth Literacy Scale for Carers
EHT: electronic health care tool
FDA: Food and Drug Administration
HIPAA: Health Insurance Portability and Accountability Act
IRB: institutional review board
NASA-TLX: National Aeronautical and Space Administration’s Task Load Index
PRIME: *P*reference *R*eporting to *I*mprove *M*anagement and *E*xperience
PSSUQ: Post-Study System Usability Questionnaire
SEQ: Single Easy Questionnaire
sGA: Simplified Geriatric Assessment
UNC: University of North Carolina
